### Implementation of interventions for occupational stress prevention

In addition to the evaluation of effectiveness, implementation research investigates the factors that affect the translation of evidence-based practices into real world settings [25]. To facilitate the implementation of stress prevention interventions in occupational settings, Nielsen and Randall [26] recommend intervention studies that include an extensive process evaluation. Proctor and colleagues [27] summarize eight outcomes for a successful implementation process: acceptability, adoption/reach, appropriateness, feasibility, fidelity/dose, costs, penetration and sustainability.

Acceptability, adoption and appropriateness are important indicators in the early phases of the implementation process. *Acceptability* is defined as the perception among stakeholders that an intervention is desirable and satisfactory [28]. It is a dynamic outcome, as acceptability can change with experience during the implementation process and can be measured with quantitative and qualitative methods. *Adoption* describes the initial decision to implement an intervention and *reach* indicates to what extent the targeted population can be reached (e.g. which MSE sign up for taking part in stress prevention programs) [29]. *Appropriateness* of an intervention describes the perceived fit of an intervention for a specific setting. It differs from acceptability as a stakeholder, e.g. an employer, and can evaluate a stress prevention program as desirable but not appropriate for their organization (e.g. due to lack of resources) [27].

Feasibility, costs and fidelity of the delivery are important indicators after the initial implementation of the intervention. *Feasibility* is related to the concept of appropriateness but measures the actual fit between the intervention and a setting rather than the perceived fit. It is usually assessed retrospectively in order to identify barriers to an effective delivery [30]. The *costs* of the intervention can be direct (e.g. purchase price of training) and indirect (e.g. time and personnel required for training) and should be measured on the side of the adopter and the provider [27]. *Fidelity* describes the extent to which an intervention was implemented as intended, for example in terms of chronological order and *dose* (amount) of the delivered components [29].

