## Methods

### Part I – Integrated web-based platform “System P”

The web-based platform “System P” includes two adapted interventions for stress prevention: 1) a web-based tool for workplace PRA and 2) a web-based SMT.

*1) Web-based tool for psychosocial risk assessment (“Workplace check”).*

The web-based tool for workplace PRA provides a simplified version of the PRA process according to the German guidelines for structural stress prevention [GDA; 34]. To promote acceptance, we avoid using the term “psychosocial risk assessment” and have replaced it by the less stigmatized term “workplace check”. The workplace check consists of three main steps: (1) Preparation, (2) Analysis and Actions, and (3) Evaluation (see Table 1). During the preparation, employers generate questionnaires for each field of activity in their enterprise to assess possible psychosocial risks. “System P” provides a pool of 55 questions that covers a wide range of psychosocial stressors. The questions cover the main areas of work-related stress (organization, workload, social support, physical environment and boundaries) based on validated PRA questionnaires [20, 35]. Optional items on specific risks related to the COVID-19 pandemic (e.g. fear of infection at work) have been added. The standard pre-selected questionnaire is a short version with nine questions on the most important stressors according to the GDA guidelines. “System P” also includes an option to select all items automatically that are recommended for a full PRA with 43 questions. Employers can select and deselect each item individually and create their own questions for specific risks in their organization. Each item from the questionnaire pool includes a question referring to the occurrence and intensity of a psychosocial stressor, one question asking about possible reasons for the stressor, and a free-text field for suggested solutions to reduce the psychosocial risk. The final PRA questionnaire can be sent to the employees directly via the tool or by copying the URL and sending it for example via email.

**Table 1 Tab1:** Contents of the web-based tool for workplace psychosocial risk assessment (PRA)

Step^**a**^	Intervention content
1	Preparation of questionnaires
2	Stressor analysis and developing actions
3	Evaluation of actions

Note: ^a^ in the official GDA guidelines, a full PRA cycle includes seven steps which have been summarized but not discarded in “System P” for the purpose of simplification

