The web-based training “GET.ON Stress” has already been evaluated showing significant effects on stress and stress-related problems like depressive symptoms as compared to controls [36–39]. It was designed to enhance two strategies of stress coping: problem-solving [40] and emotion regulation [41]. The training consists of seven sessions that participants should work on following a weekly schedule [36, 42] (see Table 2). Each session consists of general information, interactive exercises, prototype training participants – so called *personas*– who represent different stressed employee groups, quizzes, audio and video files and downloadable work sheets. In addition, at the end of sessions 2 to 6, users can choose to obtain extra information and perform short exercises about the following common stress-related topics: time management, rumination and worrying, psychological detachment from work, sleep hygiene, sleeping habit rhythm and regularity, nutrition and exercise, organization of breaks during work, and social support [42]. For this trial, we adapted “GET.ON Stress” to employees working at small businesses. Specifically, we adapted the personas within the web-based program who guide participants through the training. Personas are a well-established element of user-centered design in software engineering [43] that has also been used to tailor web-based interventions to specific target groups [44, 45]. Within “GET.ON Stress”, the personas aim to increase user engagement in the training, providing knowledge about how to complete the exercises within the training and helping users to transfer what they learn from the exercises into their daily lives; for instance, by giving examples of how employees working under similar circumstances apply a given problem-solving strategy in their daily life. Examples of the adapted personas for the MSE context can be found in Additional file 1. In addition to training content, participants can receive written feedback from an e-coach on their exercises after each training session. E-coaches are psychotherapists or master’s degree-level psychologists. Based on our experience from previous studies, we anticipate that the e-coaches will spend roughly 30 min per feedback. To improve the adherence of the participants with the training, the e-coaches will send reminders to participants any time they fail to complete a training session within 7 days. All communication between the participant and the e-coach will take place anonymously within the secured web-based platform “System P”. The duration of the intervention is completely self-paced (between 6 weeks and 6 months).

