#### Process outcomes

Acceptability: One measurement of acceptability of stress prevention interventions is the readiness for change which will be assessed by three items adapted from Hoek et al. [63]. Items are “I believe in the value of stress prevention”, “Stress prevention is positive for the organization” and “Stress prevention is necessary” and the answers range from 1 “strongly disagree” to 5 “strongly agree”. After the implementation period, we will also measure satisfaction with the intervention by asking participants to rank the usefulness of each intervention component at T2 on a 5-point scale, with a target average score of 3 or higher.

Adoption/Reach: The proportion of MSE who adopted “System P” will be calculated by dividing the number of registered MSE at T0 by the number of invited MSE during recruitment (R1). Reach will be analyzed by comparing socio-demographic characteristics of MSE that implemented “System P” with the characteristics of non-responders (using aggregated data from the recruitment partners and data from non-responder questionnaire) to see if they are representative of the population.

Appropriateness: To gain further information on appropriateness (perceived fit for the setting), we will conduct semi-structured personal interviews with employers of MSE that are registered with inter-corporate stakeholders who are unable to contact their members via email newsletters at R1 as described above. Employers will be contacted via phone by the recruitment partners and referred to the project team. They will receive access to videos sequences introducing the web-based platform in the week prior to the interview and will then be asked about aspects that they liked and disliked as well as potential barriers for the use of the platform (the interview guide can be found in Additional file 3). The platform should be regarded as appropriate by a majority of the employers.

Fidelity: To measure fidelity, we analyze usage data collected directly via “System P”. We will track data on the times of login, number of steps completed in the web-based tool for PRA (minimum 2) and the number of completed sessions in the web-based training (minimum 5). Additionally, we will ask the participants about their use of the interventions in the online questionnaires at T2 and T3 (e.g. “How much time have you spent on average for the training?”).

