Costs: The direct costs of the implementation in “System P” are none because participating organizations will not be charged for the use of the web-based platform during the study. Indirect costs will be calculated by multiplying the time spent on the platform by the average hourly salary. The hours spent logged in to the web-based platform will be monitored for employers, employee and e-coaches.

Feasibility & Sustainability: Feasibility and sustainability will be assessed by means of focus groups with a subsample of the participating MSE. All employers registered at T0 will receive an invitation to take part in the discussion about stress prevention and will be asked to describe their experience with “System P”. They will be asked to discuss barriers and facilitators for long-term implementation in their organization and suggest improvements to the web-based interventions. We will also monitor the proportion of MSE that still use the platform between T2 and T3, with a target of 20% or more.

Penetration: Penetration of the intervention within the organization will be analyzed comparing the number of registered employees who filled out the questionnaire at T1 with the number of employees reported by the employer at T1 with a target participation rate of 50% or more. We will also ask MSE during the focus groups whether new employees have received access to the platform after the implementation period to gain more information on the penetration of the interventions.

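### The cost outcome is narrower than the protocol's own definition of cost: spending on workplace actions, off-platform training work and provider direct costs are left out, so cost is understated by an unknown amount

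*Protocol article*

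**What the plan says.** **The definition.** The background section on implementation of interventions for occupational stress prevention lists cost among the outcomes of an implementation process. Its example of a direct cost is the purchase price of a training. Its example of the other kind is "indirect (e.g. time and personnel required for training". On the question of whose cost counts, the section names two parties and says that it "should be measured on the side of the adopter and the provider".

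**The measure.** The Costs paragraph under Process outcomes has three parts.
- Login time is recorded for three groups, two on the adopter side and one on the provider side. The text reads "The hours spent logged in to the web-based platform will be monitored for employers, employee and e-coaches".
- A single formula then turns this time into money, with no source named for the pay rate. It reads "Indirect costs will be calculated by multiplying the time spent on the platform by the average hourly salary".
- Nothing is added for expenditure. On that side the paragraph holds that costs "are none because participating organizations will not be charged for the use of the web-based platform during the study".

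**The work being costed.** Part I of the Methods describes two components.
- *Workplace check (PRA).* Employers plan actions and record their progress in the tool. The actions themselves take place in the enterprise. A full cycle runs from 3 to 12 months.
- *Stress management training (SMT).* There are seven sessions of about 45 to 90 minutes (Table 2), with work sheets to download and optional written feedback from an e-coach. For the latter, "we anticipate that the e-coaches will spend roughly 30 min per feedback".

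The implementation strategy adds a moderated forum and an introductory webinar given by project experts.

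**Related data.** The Fidelity paragraph adds questions at T2 and T3 about use of the interventions, for example "How much time have you spent on average for the training". Table 3 lists income, working hours and occupational position at T1. Neither source is linked to the cost formula.

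**The concern.** Cost matters more here than in many trials. The background names shortage of time, staff and money as a barrier to prevention in small enterprises. The implementation strategy rests on enterprises using the platform without extra cost, and the Conclusion describes the interventions as low-cost. The Discussion gives the implementation evaluation the same weight as effectiveness.

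The structural half of the intervention consists of changes in working conditions. If only the time spent recording those changes in the tool is counted, the labour and money behind them enter as zero by construction. Setting direct costs to none because users pay no fee also says nothing about what the provider spends. A reader of the final report could take the resulting figure for the cost of implementation when it is the cost of platform time.

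**Working it through.** The Costs paragraph gives no monetary figure, so there is nothing to reproduce. The check sets the definition beside the measure and then uses the stated times to see which parts could matter.

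**Step 1. Definition against measure**

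| Component | Called for by the definition | Captured by the Costs paragraph |
|---|---|---|
| Adopter, direct: platform fee | yes | yes, and it is truly zero in the study |
| Adopter, direct: money spent on actions | yes, if actions count as part of the intervention | no |
| Adopter, indirect: time on the platform | yes | yes, logged hours |
| Adopter, indirect: training work off the platform | yes | no |
| Adopter, indirect: staff hours on actions | yes, if actions count as part of the intervention | no |
| Provider, indirect: e-coach time | yes | yes, logged hours |
| Provider, direct: for example platform operation, forum moderation | yes | no, and the reason given for none does not apply to the provider |

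Every uncovered row is zero or positive, so each omission can only lower the reported cost.

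**Step 2. Stated times for one user of the training**
- Participant: 7 × 45 min = 5.25 h; 7 × 90 min = 10.5 h.
- E-coach, if feedback follows every session: 7 × 30 min = 3.5 h.
- E-coach share of combined hours: 3.5 / (3.5 + 5.25) = 40%; 3.5 / (3.5 + 10.5) = 25%.

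The provider time that is logged is therefore a substantial share, and it should be shown separately.

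**Step 3. Off-platform adopter time (assumed share s)**

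True time / logged time = 1 / (1 − s).

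| s | Ratio |
|---|---|
| 10% | 1 / 0.90 = 1.11 |
| 25% | 1 / 0.75 = 1.33 |
| 50% | 1 / 0.50 = 2.0 |

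The documents give no value for s.

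**Step 4. Unit cost (assumed pay ratio r, e-coach to participant)**

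This applies only if one participant rate were used for all roles, which the text neither states nor rules out. With h participant hours, the relative error is (h + 3.5) / (h + 3.5r) − 1.

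| r | h = 5.25 | h = 10.5 |
|---|---|---|
| 1.0 | 0% | 0% |
| 1.5 | 8.75 / 10.5 − 1 = −17% | 14 / 15.75 − 1 = −11% |
| 2.0 | 8.75 / 12.25 − 1 = −29% | 14 / 17.5 − 1 = −20% |

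**Step 5. Actions from the workplace check**

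The documents give no hours or expenditure for actions, so no size can be derived. Table 3 names no instrument that would collect them. The use questions under Fidelity are given only by example, so a related item may exist, but the cost formula does not draw on it.

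**The case against.** **The best defence** is that the Costs paragraph follows the definition's own examples. The purchase price is zero because nobody is charged, and time is logged for employers and employees on the adopter side and for e-coaches on the provider side. Whether workplace actions belong to the cost of implementing a platform is a choice of scope, since the definition's examples refer to training. This stands in part: it rules out calling the measure incapable. It does not explain the missing provider direct costs. Nor does it sit easily with an intervention whose structural component is the action itself.

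**Stronger readings that the documents do not support**
- *That the measure cannot capture adopter or provider cost at all.* Logged hours capture part of both.
- *That the study will find low cost whatever the truth.* No cost target, threshold or hypothesis is set. The formula gives a positive cost that rises with use, and the Conclusion's low-cost description concerns the platform as offered.
- *That uncounted action time exceeds a whole training course.* Suppose a five-person enterprise spends 15 to 30 person-hours, a figure found nowhere in the documents. That is an enterprise total and must not be set against one user's 5.25 to 10.5 h. Five completing users account for 26.25 to 52.5 h, so the ratio runs from 15 / 52.5 = 29% to 30 / 26.25 = 114%, resting wholly on the assumption.
- *That questionnaires answered by link escape the log.* The questionnaire can be distributed "by copying the URL and sending it for example via email", but whether a login is then needed is not stated.
- *That idle sessions inflate the log, or that a single salary is pooled over all roles.* How logged time is measured and where the salary comes from are not stated, and may be set in a plan not shown. These are reasons to be explicit, not errors in themselves.

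**Conclusion.** The concern holds as a point of completeness. Measured against the protocol's own definition, the Costs paragraph leaves out enterprise hours and money spent on actions, training work done off the platform, and the provider's direct costs. Each omission understates cost. The total size is unknown: the factors of 1.11 to 2.0 for adopter time rest on assumed off-platform shares of 10% to 50%, and the 11% to 29% understatement of labour cost rests on an assumed pay ratio of 1.5 to 2 and on one participant rate for all roles.

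The clearest mismatch is on provider direct costs, because the reason given for setting direct costs to none concerns adopters only. Counting action costs requires treating the actions as part of the intervention, which Part I supports. Cost is one of several process outcomes and feeds no decision rule. The change in PHQ-8 from T1 to T2 is unaffected. This is a cheap improvement, best made before any cost result is reported.

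**What to change.** 1. In the Costs paragraph, replace the statement that direct costs are none with: *no platform fee is charged; adopter spending on implemented actions and provider direct costs (for example platform operation and forum moderation) are reported*.
2. Add one short employer item at T2 and T3 on hours and money spent on actions from the workplace check.
3. Keep logged hours as the main measure of platform time. Report the self-reported training time already asked at T2 and T3 beside it as a sensitivity analysis.
4. Value time by role: T1 income and working hours for employers and employees, and a separate e-coach rate reported as provider cost.

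**Cost of the change.** Wording, one extra employer item, and the provider's own expenditure records. Income, working hours and training time are already planned. The downsides are recall error in the new item and a less favourable cost figure.

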### Analysis

#### Sample size

Power analysis has been performed with G*Power [66] for a one sample case on the primary outcome measure depressive symptoms (PHQ score). Based on the average changes in depression reported in previous research [19, 22], we estimate a medium effect size (Cohen’s d = 0.4) [67]. With a power of 0.95 and a one-sided alpha α of 0.05, this resulted in a sample size of *n* = 70 at post-intervention measurement (T2). Due to interdependencies of the observations within MSE, we multiplied n with the design effect (DE) of cluster-randomized trials (DE = 1+ (NC-1)*ICC) [68], assuming an average cluster size (NC) of 5 (average number of employees in German MSE) and an intra-class correlation coefficient (ICC) of 0.1. This results in a required sample size of *n* = 98, and a minimum number of 20 MSE. If only 2-person MSE register (NC = 2), this would result in a required sample size of *n* = 77, equaling 39 MSE. We cannot predict the actual size of the MSE (with a range from 1 to 49 employees) and how many MSE will complete post-intervention assessment (T2) but previous studies show that only one quarter of all MSE that start interventions for stress prevention complete them [69]. The goal is therefore to recruit between 80 and 150/200 MSE for the baseline measurement. In the case of more registrations, only the first 200 MSE will be considered for the subsequent analyses.

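### The 0.95 power claimed for 98 people in 20 MSE assumes equal-sized enterprises, so it is not assured at that minimum or at the 80-MSE recruitment floor

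*Protocol article*

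**What the plan says.** All of the following is in the Sample size section of the protocol article, unless another section is named.

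- The calculation is "for a one sample case on the primary outcome measure depressive symptoms (PHQ score"), and the planned effect is given as "we estimate a medium effect size (Cohen’s d = 0.4").
- The error rates are set by "With a power of 0.95 and a one-sided alpha α of 0.05". This gives n = 70 at T2.
- To allow for clustering within MSE, 70 is multiplied by a factor named as the "design effect (DE) of cluster-randomized trials (DE = 1+ (NC-1)*ICC"). The cluster size entered in it comes from "assuming an average cluster size (NC) of 5 (average number of employees in German MSE"). The strength of clustering is taken as "an intra-class correlation coefficient (ICC) of 0.1".
- The outcome of this step is introduced by the words "This results in a required sample size of", and the figure given is 98 people, in no fewer than 20 MSE. The only alternative takes every MSE to have two people, giving 77 people in 39 MSE.
- The paragraph then says: "We cannot predict the actual size of the MSE (with a range from 1 to 49 employees").
- About one quarter of MSE that start are expected to complete, and the baseline goal is 80 to 150/200 MSE.

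The section on analysis of quantitative data plans a multilevel analysis for the effect evaluation. No measure of variation in cluster size appears anywhere.

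**The concern.** The design effect 1 + (NC − 1) × ICC is exact when every cluster contributes the same number of people. The document describes something else: enterprises of 1 to 49 employees, averaging five, with sizes that the authors say they cannot foresee. For a fixed number of people in a fixed number of clusters, unequal sizes carry less information about the mean than equal ones. The direction of the error at 98 people in 20 MSE is therefore known without any outside figure.

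The one sensitivity case does not cover this. Setting NC = 2 lowers the design effect to 1.1, so it explores only the favourable side.

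The pair of 98 people and 20 MSE also sets the recruitment floor: 20 completing MSE divided by one quarter gives 80. A team that stops at 80 has met its stated goal with almost no margin for variation in size.

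**Working it through.** **Inputs from the protocol.** d = 0.4; one-sided alpha 0.05; power 0.95; NC = 5; ICC = 0.1; one quarter of MSE completing. **Assumed, because the document gives no value:** the CV of cluster size, shown at 0.6, 1.0 and 1.3.

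**1. The plan's own figures.** A one-sample t-test with the noncentral t distribution gives power 0.952 at n = 70. DE = 1 + (5 − 1) × 0.1 = 1.4; 70 × 1.4 = 98; 98/5 = 19.6, so 20 MSE. With NC = 2, DE = 1.1; 70 × 1.1 = 77; 77/2 = 38.5, so 39 MSE. Every figure reproduces.

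**2. Direction.** Under a multilevel model with known ICC, an MSE with m people contributes m/(1 + (m − 1) × ICC) to the effective sample size. This function is concave in m, so for a fixed total and a fixed number of MSE the sum is largest when all sizes are equal. Slack from rounding is very small: an effective n of 69 already gives 0.950 only to three decimals (0.94996).

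An invented but concrete set of 20 MSE totalling 98 people (eight of 2, six of 4, three of 6, two of 10, one of 20; CV 0.86) shows the effect:
8 × 1.818 + 6 × 3.077 + 3 × 4.000 + 2 × 5.263 + 6.897 = 62.4, which gives power 0.93.

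**3. Planned multilevel analysis.** Sets of 20 sizes were simulated (lognormal, rounded, clipped to 1–49, mean about 5), the effective n was summed as in step 2, and power was averaged over the sets.

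| Realised CV | Mean effective n, total scaled to 98 | Power |
|---|---|---|
| 0.60 | 65.8 | 0.94 |
| 0.97 | 61.7 | 0.92 |
| 1.29 | 58.2 | about 0.90 |

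The last row is 0.906 with the total scaled to 98, and 0.901 with the total left to vary around 100.

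**4. Conservative bound: plain person mean.** DE = 1 + [(1 + CV²) × NC − 1] × ICC, with effective n = 98/DE and required n = 70 × DE.

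| CV | DE | Effective n at 98 | Power at 98 | Required n | MSE at 5 each |
|---|---|---|---|---|---|
| 0.6 | 1.58 | 62.0 | 0.93 | 111 | 23 |
| 1.0 | 1.90 | 51.6 | 0.88 | 133 | 27 |
| 1.3 | 2.245 | 43.7 | 0.83 | 158 | 32 |

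**5. Recruitment goal, at five analysed people per completing MSE.**
- 80 MSE: 80 × 0.25 = 20 completing, about 100 people. Power is 0.956 with equal sizes and 0.889 at CV 1.0 on the person-mean formula. The multilevel figures are those of step 3.
- 150 MSE: 37.5 completing, about 188 people. Person-mean power is 0.989 at CV 1.0 and 0.962 at CV 1.5.
- 200 MSE: 50 completing, 250 people. Person-mean power is 0.998 at CV 1.0 and 0.989 at CV 1.5.

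**The case against.** Four points can fairly be made for the plan.

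*The arithmetic is right.* It is. The problem is the formula chosen for the setting described, not a miscalculation.

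*No CV is given, so a shortfall cannot be asserted.* This limits the size of the point, not its direction. Even on the person-mean formula the drop stays within about 2 percentage points up to a CV of about 0.59. A reader might infer that the trial is seriously underpowered, for example from the person-mean power of 0.79 at CV 1.5. The documents do not support that: they give no CV, and the person-mean formula is not the planned analysis. Multilevel weighting recovers much of the loss.

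*Headcount is not the number analysed.* The range of 1 to 49 is the eligibility range for employees, and the Penetration paragraph targets participation of 50% or more. With NC = 2.5 and CV 1.0, DE = 1 + (2 × 2.5 − 1) × 0.1 = 1.40, and the required n is again 98. So a reader should not infer that 98 people is too few under every cluster size. But 98 people at 2.5 each means 98/2.5 = 39.2, or about 40 MSE. The stated pair, 98 people in 20 MSE, fixes the mean near five and is not rescued. Nor is the floor of 80: 20 completing MSE at 2.5 each is 50 people, with power of about 0.83 even with equal sizes.

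*The recruitment goal has room.* This stands for 150 to 200 MSE, provided about five people per completing MSE are analysed. It does not stand for the lower bound of 80.

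**Conclusion.** The claim of 0.95 power for 98 people in 20 MSE is wrong as written for the enterprises that the section itself describes. At that minimum, and at the floor of 80 MSE, 0.95 is not assured. Under the planned multilevel analysis, power is more likely about 0.90 to 0.94, with 0.83 to 0.93 as a conservative person-mean bound, for an assumed CV of 0.6 to 1.3. These figures keep the plan's d = 0.4, ICC = 0.1 and mean of five, and a roughly lognormal size distribution for the multilevel case. The consequence is a modest overstatement of power at the minimum. It does not show that the design fails, and it does not affect the upper part of the recruitment goal if about five people per completing MSE are analysed.

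**What to change.** In the Sample size section:

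- State an assumed CV range for the number of analysed people per MSE (for example 0.6 to 1.3), labelled as an assumption.
- Use one calculation throughout, preferably the one that matches the multilevel analysis: effective n as the sum of m/(1 + (m − 1) × ICC). Restate the power at 98 people in 20 MSE as about 0.90 to 0.94.
- Alternatively, give the person-mean formula as a conservative bound, with its own results: power 0.93 / 0.88 / 0.83, or required n of 111 / 133 / 158. The two sets of figures should not be mixed, because the person-mean formula does not yield the 0.90 to 0.94 range.
- Recheck the figure once from the observed number of participants per MSE.

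The cost is about two sentences and a slightly less favourable stated power. Even the conservative requirement of 23, 27 or 32 completing MSE means 92, 108 or 128 at baseline with one quarter completing (multiply by 4). That lies inside the stated goal of 80 to 200, so no recruitment beyond it is needed.

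### The lower recruitment bound of 80 MSE counts every employee of a retained MSE as a T2 respondent; at the plan's own 50% participation target, power there is about 0.83 to 0.905, not 0.95

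*Protocol article*

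**What the plan says.** All the planning figures are in the Sample size section of the protocol article. The effect size is given as "we estimate a medium effect size (Cohen’s d = 0.4". "With a power of 0.95 and a one-sided alpha α of 0.05", "this resulted in a sample size of *n* = 70 at post-intervention measurement (T2".

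This number is inflated by the design effect 1 + (NC − 1) × ICC, "assuming an average cluster size (NC) of 5 (average number of employees in German MSE", and with "an intra-class correlation coefficient (ICC) of 0.1". The result is 98 people in at least 20 MSE. A second case, in which only two-person enterprises register, gives 77 people in 39 MSE.

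The section then says that MSE sizes cannot be predicted ("with a range from 1 to 49 employees") and cites earlier work in which a quarter of MSE that started stress prevention completed it. From this it draws the recruitment target: "The goal is therefore to recruit between 80 and 150/200 MSE for the baseline measurement". Analysis is limited to the first 200 MSE.

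Under Process outcomes, penetration compares the registered employees who completed the T1 questionnaire with the headcount reported by the employer, "with a target participation rate of 50% or more". The two sections do not refer to each other.

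**The concern.** The primary outcome is an individual self-rating (PHQ-8), so the unit that carries power is the person who answers at T2. The cluster size used both in the design effect and in converting people to MSE is headcount, not respondents. The only loss allowed for is loss of whole enterprises, so a retained MSE is treated as supplying all of its staff.

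Elsewhere the plan expects less. Half of the employees at T1 counts as reaching the target, and Study limitations foresees employees refusing parts of the programme and unexplained dropouts.

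A team could therefore recruit its stated minimum, see the retention it assumed, reach its own penetration target, and still have too few T2 respondents for the stated power on the primary outcome.

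**Working it through.** **Inputs from the protocol article.** d = 0.4; one-sided α = 0.05; power 0.95; ICC = 0.1; average headcount 5; MSE completion 25% (all Sample size); penetration target 50% at T1 (Process outcomes). Power is for a one-sample t-test by the noncentral t distribution, with effective n = N / DE and DE = 1 + (NC − 1) × 0.1.

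**1. The plan's own figures reproduce.**
- Unclustered: n = 70 gives power 0.952.
- NC = 5: DE = 1.4; 70 × 1.4 = 98; 98 / 5 = 19.6, so 20 MSE; 20 / 0.25 = 80.
- NC = 2: DE = 1.1; 70 × 1.1 = 77; 77 / 2 = 38.5, so 39 MSE; 39 / 0.25 = 156.

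The 80 and 156 are not derived line by line in the article, but 80 equals 20 / 0.25 exactly. This is why the 25% is read here as T2 retention of MSE.

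**2. Power at 80 MSE (20 retained) for different numbers of respondents per MSE.**

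| Respondents per MSE (NC) | Corresponds to | People at T2 | DE | Effective n | Power |
|---|---|---|---|---|---|
| 5 | all employees | 100 | 1.40 | 71.4 | 0.956 |
| 4.5 | 90% of employees | 90 | 1.35 | 66.7 | 0.944 |
| 4 | 80% of employees | 80 | 1.30 | 61.5 | 0.93 |
| 3.5 | 50% of employees plus the employer | 70 | 1.25 | 56.0 | 0.905 |
| 2.5 | 50% of employees | 50 | 1.15 | 43.5 | 0.83 |

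With employees only, about 95% participation (NC = 4.75) is needed for 0.95. The lower bound has almost no slack. The smaller design effect of smaller clusters is already credited in these rows.

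**3. MSE needed for 0.95 at the 50% target.**
- NC = 2.5: 70 × 1.15 = 80.5, so 81 people; 81 / 2.5 = 32.4, so 33 MSE at T2; 33 / 0.25 = 132 at baseline.
- NC = 3.5: 70 × 1.25 = 87.5, so 88 people; 87.5 / 3.5 = 25 MSE at T2; 25 / 0.25 = 100 at baseline (rounding up to 88 people first gives 26 MSE and 104).

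**4. Higher in the range.** At NC = 2.5, 150 MSE give power 0.97 and 200 give 0.99.

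**The case against.** The strongest reply has five parts.

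- **No sum is wrong, and 0.95 is attached to 98 or 77 people at T2, not to 80 MSE.** The first half is true. But the recruitment goal is presented as following from those numbers, so its lower end is offered as sufficient.
- **The target is a range that already covers smaller clusters.** This holds for the upper part, since 132 lies inside it. It does not rescue 80: the plan's own two-person case needs 156 MSE, and at NC = 2 the bound of 80 gives 40 people, effective n 36.4 and power 0.76.
- **The 50% is a minimum measured at T1, not a forecast.** This stands. The 0.83 to 0.905 is power when the target is just met. Individual dropout between T1 and T2 works the other way.
- **Employers also answer the questionnaires.** This stands, and it is why 0.905 is given beside 0.83.
- **A quarter is the share completing an intervention, not the share answering at T2.** This stands as a caveat. The planned comparison with people who completed one step or less implies that some non-completers supply T2 data. If 35% of MSE responded at T2 (an assumption), 80 MSE would give 28 MSE at T2 and power of about 0.925 (NC 2.5) or 0.97 (NC 3.5).

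Two stronger readings are tempting but not supported. A reader might set 50 and 70 respondents against 98 and infer that only about half to 70% of the required sample is reached. But 98 is the requirement at NC = 5. Against 81 and 88, the fractions are 62% and 80%. A reader might also infer that two-person MSE at 50% participation breach the 200 cap: one respondent per MSE needs 70 at T2, or 280 at baseline. That requires employers to be left out. With the employer responding and the one employee at 50%, NC = 1.5, DE = 1.05, 73.5 / 1.5 = 49 MSE, and 49 / 0.25 = 196, which is under the cap. Figures for unequal cluster sizes, or for a particular individual T2 response rate, would need inputs that the article does not give.

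**Conclusion.** The concern holds for the lower bound only. The recruitment minimum of 80 MSE delivers the stated 0.95 only with near-complete participation inside each retained MSE, and the plan sets its own participation target far below that. At that target, power is about 0.83 (employees only) to 0.905 (with one employer per MSE), a loss of roughly 5 to 12 percentage points. At 80% participation of employees it is 0.93.

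This rests on 25% MSE retention at T2, five employees per MSE, ICC 0.1, participation just at 50%, and no further individual dropout. The last assumption is favourable to the plan; the retention figure may be unfavourable to it.

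The documents do not support calling the whole range inadequate. From about 132 MSE upwards it suffices for MSE with five employees. The point is worth correcting because the bound lacks a property the plan attributes to it. It does not undermine the design or the analysis, and power of 0.83 to 0.905 may be acceptable if it is stated.

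**What to change.** In the Sample size section, define NC as the expected number of T2 respondents per MSE (headcount times expected participation, plus the employer if counted), and use it both in the design effect and in converting people to MSE. Then do one of the following:

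- keep 80 as the lower bound and state that its power is about 0.83 to 0.90 when participation just meets the 50% target; or
- raise the lower bound within the existing 80 to 200 range, to about 132 MSE, or about 100 if each employer is expected to respond.

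In either case, state the recruitment goal as individual T2 respondents, about 81 to 98 depending on respondents per MSE. Progress can then be judged on the unit that carries the power. Say also whether the one-quarter figure is meant as T2 questionnaire response or as completion of the intervention.

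The cost is a rewritten paragraph. No recruitment beyond the stated 200 MSE is needed, and the outcome and analysis stay as they are. The first option makes the stated power at the lower bound less favourable; the second commits the team to more MSE than its present minimum.
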